#### **9.4.2 EVALUATION OF SUCCESS OF BLINDING**

Not applicable.

#### **9.4.3 BREAKING THE STUDY BLIND/PARTICIPANT CODE**

Not applicable.

### **10. DATA HANDLING AND RECORD KEEPING**

#### **10.1 Data Collection and Management Responsibilities**

Data collection is the responsibility of the Tanzanian trial staff at the site under the supervision of the site PI. The Tanzanian PI is responsible for ensuring the accuracy, completeness, legibility, and timeliness of the data reported. Data will largely be collected using tablet computers using a digital data collection application, such as CommCare app. This data will be automatically uploaded to the application cloud server will be encrypted and password-protected in accordance to the Level 4 data security and storage regulations. Data will be uploaded nightly to the application server using Wi-Fi. Data collected in this way will include AEs, adverse reactions, clinical test and laboratory data.

## **10.2 Study Records Retention**

All study records will be retained at the Tanzanian research site and at Heidelberg University for 5 years. Paper records (i.e. signed consent forms) will be stored either in a locked cabinet or will be scanned and kept on an encrypted storage device in Tanzania. Electronic records will be maintained on an encrypted storage device. Anonymized data and all anonymized study records at both Heidelberg and MUHAS will be retained for 5 years after study closure.

## **10.3 Protocol Deviations**

A protocol deviation is any noncompliance with the clinical trial protocol, GCP, or MOP requirements. The noncompliance may be either on the part of the participant, the investigator, or the study site staff. As a result of deviations, corrective actions are to be developed by the site and implemented promptly. These practices are consistent with ICH E6:

- 4.5 Compliance with Protocol, sections 4.5.1, 4.5.2, and 4.5.3
- 5.1 Quality Assurance and Quality Control, section 5.1.1
- 5.20 Noncompliance, sections 5.20.1, and 5.20.2.

It is the responsibility of the site to use continuous vigilance to identify and report deviations within 3 working days of identification of the protocol deviation, or within 7 working days of the scheduled protocol-required activity. Protocol deviations must be sent to the local IRB per their guidelines. The Tanzanian site PI and Tanzanian healthcare providers are responsible for knowing and adhering to their IRB requirements.

## **10.4 QUALITY ASSURANCE AND QUALITY CONTROL**

QC procedures will be implemented beginning with the data entry system and data QC checks that will be run on the database will be generated. Any missing data or data anomalies will be communicated to the site(s) for clarification/resolution.

The investigational site (Dar es Salaam) will provide direct access to all trial related sites, source data/documents, and reports for the purpose of monitoring and auditing by all study

sponsors, and inspection by local and regulatory authorities. At no time will Heidelberg study team members have access to identifiable data.

## 10.5 ANALYSIS DATASETS

The primary dataset for analyses relating to primary endpoint 1 will be an Intention-to-Treat (ITT) analysis dataset, containing all participants who were eligible and thus randomized. The primary dataset for all analyses relating to the primary endpoint 2 and secondary endpoints will be a Modified Intention-to-Treat (MITT) analysis dataset, containing all randomized participants who initiated PrEP. Tanzanians will do the main part of data analyses. There are Tanzanians who will use this data for their PhD studies at Heidelberg University. These Tanzanians will need support on scholarly works from their PhD supervisors at Heidelberg University. Therefore all datasets provided to Heidelberg for analysis will be de-identified.

### 10.5.1 DESCRIPTION OF STATISTICAL METHODS: GENERAL APPROACH

This study will be a parallel group randomized controlled trial, in which individuals are randomized independently into two interventions: receiving workplace-based PrEP vs. standard of care facility-based provision, and receiving the PrEP champion intervention or not.. All inferential tests will use a type-I error rate of 5% and will be two-tailed.

For univariate descriptive statistics, categorical data will be presented as percentages and continuous data as means and standard deviations (if normally distributed) and medians and interquartile ranges (otherwise).

Covariates for analysis of exploratory endpoints and secondary analysis of primary endpoints will be defined in the later SAP.

### 10.5.2 ANALYSIS OF THE PRIMARY EFFICACY ENDPOINT(S)

For **primary endpoint 1**, the proportion of eligible individuals who initiate PrEP will be measured based on observation of PrEP initiation at Visit 1. The initiation proportion secondary endpoint will be analysed as such using a two-sample test of proportion. The analysis set for this endpoint will be the ITT dataset including anyone who was screened, found to be eligible for PrEP and was randomized.

For **primary endpoint 2**, TDF level will be measured using urine-based TDF level estimation assay. TDF level will be analysed as a continuous measure in single nanograms per milliliter (ng/mL) and will be a single endpoint measure. The primary endpoint will be assessed using a two-sample t-test of log transformed data where the continuous outcome is TDF level and two exposure categories will be study group (workplace-based or facility-based PrEP). The analysis set for this endpoint will be the MITT dataset including anyone who initiated PrEP based on observed taking of their Day 0 pill.

For the test outcome, we will assume that women who default from treatment or are lost to follow-up will have TDF levels of zero.

### 10.5.3 ANALYSIS OF THE SECONDARY ENDPOINT(S)

**Secondary endpoint 1:** The number of refills per initiated participant will be measured as the number of return visits (0-6) at which emtricitabine/tenofovir disoproxil was dispensed to the participant. The endpoint will be assessed twice, in both cases using one-way ANOVA. In the first instance, the likelihood of reporting 0,1,2,3,4,5 or 6 refills will be compared between the facility- and workplace-based groups; in the second instance, the likelihood will be compared between being or not being part of the omni-channel PrEP Champion intervention.

The analysis set for this endpoint will be the MITT dataset including anyone who initiated PrEP based on observed taking of their Day 0 pill.

The secondary analysis will involve no covariates; if preliminary analysis finds covariate imbalance, an ordered logistic regression model adjusting for imbalanced covariates will be run. The list of potential covariates that will be assessed will be specified in the SAP. Results will be presented as odds ratios with a 95% confidence interval.

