## **Randomization 2: Omni-channel PrEP Champion**

We will randomly assign PrEP study participants into two groups. In the intervention group participants will be provided access to the support by an omni-channel PrEP Champion, to help participants adhere to their PrEP routine. Physical support will be provided through group or individual meetings when they come for PrEP refills whereas; virtual support will be via SMS, calls, WhatsApp groups or individual digital conversations. Additionally, clients will receive the national standard of care support, which includes reminders via SMS and phone calls through the health care provider. The PrEP Champions will regularly share informative standardized media including short, Kiswahili animated videos about PrEP use and adherence, essential PrEP messages, pictures, and gifs about PrEP. The media will be developed collaboratively with the National AIDS Control Program (NACP) staff and pre-tested before they are used in the trial. Participants will also be able to ask questions and discuss with and support each other. The WhatsApp messages and physical meetings will be moderated by the trained PrEP Champions. To share the digital information, the PrEP Champions will receive monthly internet bundles from the study team.

In the control group participants will receive the national standard of care, which includes refill reminders via SMS, phone calls and WhatsApp messages as done in the national standard of care. This randomization will be at the individual level. Those who are willing to participate will sign an additional consent form. Participants will be able to drop out at any time and feedback on the utility of the omni-channel PrEP Champions program will be solicited throughout the study. If a participant does not respond to the standard of care reminders and does not show up at her scheduled appointment, the study team will inform the facility or community PrEP lead about the non-responders for further follow up according to the national guidelines.

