| G.4      | Stationeries & photocopying of tools                       | Once                 | 1          | 1         | 1      | 25        | 25         | 100%     | 25                |
|          | Subtotal Barmapping Costs                           |                      |            |           |        |           |            |          | 1.105      |
|          | PrEP Champion intervention                          |                      |            |           |        |           |            |          |                   |
|          | Training of PrEP champions                          |                      |            |           |        |           |            |          |                   |
|          | Venue                                                      | Daily                | 1          | 3         | 1      | 85        | 255        | 100%     | 255               |
|          | Travel and half perdiem for PrEP champions                 | Daily                | 15         | 3         | 1      | 20        | 900        | 100%     | 900               |
|          | Trainers allowances                                        | Daily                | 8          | 3         | 1      | 50        | 1.200      |          | 1.200             |
|          | Refreshments                                               | Daily                | 24         | 3         | 1      | 10        | 720        |          | 720               |
|          | Sub Total Training                                         |                      |            |           |        |           | 3.075      |          | 3.075             |
|          | Monthly salary                                      |                      |            |           |        |           |            |          |                   |
|          | Monthly Salaries for PrEP champions                        | Montly               | 15         | 1         | 9      | 120       | 16.200     |          | 16.200            |
|          | Total for PrEP champion intervention                |                      |            |           |        |           | 19.275     |          | 19.275            |
| H | Total Direct Costs                                  |                      |            |           |        |           |            |          | 151.414    |

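### The Champion comparison of refills ignores clustering by Champion; if Champion or group effects vary, the planned one-way ANOVA modestly exceeds its 5% error level

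*Protocol*

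**What the plan says.** The second randomization assigns women, not bars: "This randomization will be at the individual level" (Section 4.1, Randomization 2). In the intervention arm, part of the support is delivered jointly. "Physical support will be provided through group or individual meetings when they come for PrEP refills", virtual support may run through WhatsApp groups or one-to-one contact, and "Participants will also be able to ask questions and discuss with and support each other". On who leads this: "The WhatsApp messages and physical meetings will be moderated by the trained PrEP Champions". Section 3 (secondary objective 1) refers to a Champion responsible for the participant, but no rule links women to Champions.

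The number of Champions does not appear in the methods. The budget in Annex 1 has a line "Monthly Salaries for PrEP champions" with a quantity of 15. The table in Section 9.4.1 puts 40 + 40 = 80 women in the Champion arm and 40 + 40 = 80 in the control arm.

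For refills, Section 10.5.3 states: "The endpoint will be assessed twice, in both cases using one-way ANOVA", once by delivery arm and once by Champion arm, and adds that "The secondary analysis will involve no covariates". The only fallback is an ordered logistic model for imbalanced covariates. Section 10.5.1 states: "All inferential tests will use a type-I error rate of 5% and will be two-tailed". Clustering is allowed for only in the sample size (Section 9.3), and there only by bar.

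**The concern.** A one-way ANOVA with two groups is the pooled two-sample t-test. It takes every woman as an independent observation. Women who share a Champion, or a group in which they encourage each other, may have similar refill counts, and the in-person meetings take place at the refill visits that the endpoint counts. Control women have no such link. The design is therefore partially nested: correlated observations in one arm, none from this source in the other. Individual randomization balances the arms at the start, but it does not remove correlation that arises afterwards from shared delivery.

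Section 4.3.2 uses refills to evaluate secondary objective 1. A few unusually good or poor Champions could move the mean of the whole arm, and the planned test would read that as evidence about the programme rather than about those Champions. The protocol names the test itself and leaves to the SAP only the list of potential covariates, so this is a choice already made.

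**Working it through.** **Inputs.** Women per arm: 80 and 80 (Section 9.4.1). Champions: 15 (Annex 1 only). Level: two-sided 0.05 (Section 10.5.1). ICC: none is given for Champions. I use 0.02, 0.05 and 0.09, the non-zero values that Section 9.3 tabulates for bars in the initiation table; applying them to Champions is an assumption.

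**1. The protocol's own figure.** Section 9.3 gives 160 women for 80 versus 60 ng/mL, SD 0.6 on the log scale and ICC 0.02.
- Log means 4.38 and 4.09, difference 0.29. An exact two-sample t-test with 80% power needs 69 per arm, 138 in total.
- Design effect for bars: 1 + ((1 + CV²)·m − 1)·ICC = 1 + ((1 + 0.24²)·8.25 − 1)·0.02 = 1.1545.
- 69 × 1.1545 = 79.7, rounded up to 80 per arm: 160 in total. It reproduces.
- At the expected initiation rates, 800 × 0.10 = 80 and 320 × 0.25 = 80 women enter the two delivery arms. Each splits 40/40 by Champion, which gives 80 versus 80.

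The bar design effect is the only clustering allowance in the document. It does not cover Champions.

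**2. Error rate of the planned ANOVA.** Mean caseload m = 80/15 = 5.33.
- Design effect in the Champion arm: D = 1 + (m − 1)·ICC. In the control arm, from this source: 1.
- True variance of the difference divided by the ANOVA variance: R = (D + 1)/2.
- True two-sided error: 2·(1 − Φ(1.96/√R)).

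| ICC | D | √R (factor by which the SE is too small) | True error | Simulated, continuous outcome | Simulated, 0–6 count |
|---|---|---|---|---|---|
| 0 | 1.000 | 1.00 | 5.0% | 5.1% | 4.9% |
| 0.02 | 1.087 | 1.02 | 5.5% | 5.6% | 5.4% |
| 0.05 | 1.217 | 1.05 | 6.3% | 6.2% | 6.0% |
| 0.09 | 1.390 | 1.09 | 7.3% | 7.5% | 7.2% |

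The simulations used 40,000 trials per setting, with Champion effects varying around a mean of zero and caseloads of 5 or 6 women.

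**3. Does allowing for Champions repair it?** In the same simulated trials, a test on Champion means against individual controls with Satterthwaite degrees of freedom rejected in 4.9% to 5.2%. These simulations contained no bar effects, so they check the Champion part of the remedy only.

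**The case against.** The strongest reply is that women are randomized individually, so the ANOVA is valid under the plain null. That is right as far as it goes: if Champions changed no woman's refills, the test would hold about 5%. A reader might infer that the 5% level is certainly broken; the documents do not support that. The excess appears only when Champion or group effects vary around a zero average.

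A second reply is that the excess is small. At an ICC of 0.02, the protocol's planning value for bars, it is about half a percentage point, and some women may have mainly one-to-one contact, since the channel depends on smartphone ownership and preference. This also stands. A reader might be drawn to much larger figures: four groups of 20 women would give 7.2%, 10.7% and 15.0% at the three ICCs. Those are hypothetical, because the protocol states neither the number nor the size of any groups.

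Third, a reader might infer that this test decides whether the programme is rolled out. Section 3 ties wider roll-out to the interviews, and names self-reported adherence as the effectiveness outcome for this objective. Section 10.5.3 states no test for that outcome, so the point concerns refills only.

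Fourth, treating control women as fully independent would itself be incomplete, because women in both arms share bars. That is accepted and shapes the remedy.

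What the replies do not remove is that the named test, and its ordered logistic fallback, have no term for clustering that the protocol's own description of the intervention makes likely.

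**Conclusion.** The point holds in a conditional and modest form. Section 10.5.3 fixes an analysis that treats Champion-arm women as independent although they share Champions and, in part, groups. If those effects vary, the standard error is too small by about 2% to 9% and the two-sided error is about 5.5% to 7.3%, instead of 5%, for ICCs from 0.02 to 0.09.

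This rests on three assumptions: that 15 Champions, a number found only in the budget, carry even caseloads; that the bar ICC range is a fair guide for Champions; and that the Champion, not a larger group, is the effective cluster. Fewer active Champions or larger groups would raise the error by an amount the documents do not allow one to state. It affects one comparison of a secondary endpoint and neither primary endpoint.

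**What to change.** For the Champion comparison of refills in Section 10.5.3, replace the one-way ANOVA with a partially nested model that has:
- a random effect for Champion (or for group, if groups are the unit of delivery) in the intervention arm only;
- a bar-level random effect, or a bar-robust error, for women in both arms;
- a term for delivery arm (workplace or facility);
- small-sample degrees of freedom (Kenward-Roger or Satterthwaite).

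If the ordered logistic fallback is kept, it needs the same allowance for clustering.

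Record each woman's Champion, and her group if she has one, during the trial, since it may not be possible to reconstruct this later. State in the methods the number of Champions and how women are linked to them.

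The cost is a change of wording in the protocol and SAP, one more identifier to collect, and a slightly wider confidence interval for the Champion effect.

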### 10.5.4 ADHERENCE AND RETENTION ANALYSES

Adherence and retention form an integral part of the primary and secondary endpoint analyses, and are thus described in Sections 9.4.2 and 9.4.3 above.

### 10.5.5 BASELINE DESCRIPTIVE STATISTICS

All intervention groups will be compared on baseline characteristics, including demographic, behavioral and laboratory measurements, using proportions (categorical variables), means and standard deviations (continuous, normally distributed variables) and medians and interquartile ranges (continuous, non-normally distributed variables). The list of variables that will be assessed will be specified in the SAP. Inferential tests to detect baseline imbalance will be conducted: two-sample test of proportion (binary variables),  $\chi^2$  tests (multi-category variables) and t-tests or Wilcoxon Rank Sum tests (continuous data).

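### Refill analysis (secondary endpoint 1): whether an adjusted model is run, and for which covariates, depends on baseline imbalance found in the data, and the reported effect measure is left unclear

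*Protocol*

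**What the plan says.** Four parts of the protocol bear on this point.

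- **Section 10.5.5** (baseline statistics): "Inferential tests to detect baseline imbalance will be conducted". It lists two-sample tests of proportion, chi-square tests, and t or Wilcoxon tests. The list of variables is left to the SAP.
- **Section 10.5.1** (general approach): "All inferential tests will use a type-I error rate of 5% and will be two-tailed".
- **Section 10.5.3** (refills, secondary endpoint 1): "The endpoint will be assessed twice, in both cases using one-way ANOVA", once for workplace versus facility and once for PrEP Champion versus none. It continues: "The secondary analysis will involve no covariates"; "if preliminary analysis finds covariate imbalance, an ordered logistic regression model adjusting for imbalanced covariates will be run". Then: "The list of potential covariates that will be assessed will be specified in the SAP". It ends: "Results will be presented as odds ratios with a 95% confidence interval".
- **Section 10.5** (datasets): secondary endpoints use the modified intention-to-treat set, "containing all randomized participants who initiated PrEP".

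The two primary endpoints are not covered by this rule. Section 10.5.2 gives each a single unadjusted two-sample test.

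**The concern.** A baseline significance test asks whether chance can explain a difference between groups. After proper individual randomisation the answer is known to be yes. The test also does not show whether a variable predicts refills, which is the reason to adjust for it. A rule that adjusts only for variables flagged in this way can leave out a strong predictor that misses the threshold and include an irrelevant variable that reaches it.

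Here the flag also appears to have consequences. It decides whether the ordered logistic model is fitted and what goes into it. The ANOVA compares mean refill counts, while the ordered model gives an odds ratio. A reader of section 10.5.3 cannot tell in advance which result answers secondary endpoint 1.

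**Working it through.** The protocol states no figure on this point, so there is nothing of its own to reproduce.

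**1. What is fixed and what depends on the data**

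| Element | Where | Status |
|---|---|---|
| Unadjusted ANOVA, both comparisons | 10.5.3 | Fixed |
| Candidate covariates | 10.5.3, 10.5.5 | Left to the SAP, so can be fixed in advance |
| Whether an adjusted model is run | 10.5.3 | Depends on observed imbalance |
| Which candidates enter it | 10.5.3 | Only those found imbalanced |
| Criterion for imbalance | Not in 10.5.3 | Inferred from 10.5.5 (tests whose purpose is to detect imbalance) and 10.5.1 (two-sided 5%) |
| Effect measure | 10.5.3 | Odds ratio promised; the ANOVA does not give one |
| Whether the ordered model replaces or supplements the ANOVA | 10.5.3 | Not stated |

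**2. PrEP Champion comparison: how often chance triggers the rule**

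Enrolled women are randomised individually (section 4.1). Apart from any drop-out between randomisation and first dose, a significant baseline difference is therefore chance. With k independent variables tested at 5%, the probability of at least one flag is 1 − 0.95^k. The protocol gives no k, so a range is assumed:

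- k = 5: 1 − 0.95^5 = 0.226
- k = 10: 1 − 0.95^10 = 0.401
- k = 20: 1 − 0.95^20 = 0.642

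Correlated variables would make these figures lower.

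**3. Workplace versus facility: a different problem**

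The analysis set is formed after randomisation, by initiation. Section 9.3 assumes 25% of 320 and 10% of 800, that is 80 and 80 women. The women who start under the two offers may truly differ, so the figures in step 2 do not apply.

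- *Sensitivity of the screen.* For 80 versus 80, the standard error of a standardised difference is √(2/80) = 0.158. A true difference of 1.96 × 0.158 = 0.31 SD is flagged only about half the time. For 80% power the difference must be (1.96 + 0.84) × 0.158 = 0.44 SD. Smaller real differences will often go unflagged and so unadjusted.
- *Ignoring bars.* The listed tests make no allowance for clustering. With 8.25 women per bar (section 9.3), expected initiators are 8.25 × 0.25 = 2.06 per workplace bar and 8.25 × 0.10 = 0.83 per facility bar. The design effect is 1 + ((1 + 0.24²)m − 1) × ICC. At m = 2.06 it is 1.024 for ICC 0.02 and 1.106 for ICC 0.09, the non-zero range of the initiation table, assumed here to hold for baseline variables. The actual level, 2(1 − Φ(1.96/√DE)), is then 5.3% to 6.2%. At 0.83 per bar there is essentially no inflation. The effect is small.

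**4. Type I error of the refill test**

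Null trials of 80 versus 80 women were simulated, with a 0–6 outcome, 5, 10 or 20 covariates, covariate R² of 0.1, 0.3 or 0.5, and 6,000 runs per setting. Linear adjustment stood in for the ordered model.

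| Rule | Type I error |
|---|---|
| Adjust only for flagged covariates; only the final model counts | 3.5% to 5.0% |
| As above, but either model may be claimed | 5.0% to 6.0% |
| All covariates fixed in advance | 4.4% to 5.3% |

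The data-driven rule is mostly conservative when only the final model counts, and slightly liberal when either may be claimed.

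**The case against.** The strongest reply is that section 10.5.3 makes the ANOVA unconditional and only adds a further model. The candidate list is deferred to a SAP that section 9.1 requires before enrolment, and only one secondary endpoint is touched. Much of this stands, and it limits what can be said.

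- A reader might infer that imbalance switches the analysis from ANOVA to ordered logistic regression. The text does not say so. An added sensitivity analysis fits the wording, although the closing promise of odds ratios pulls the other way. The passage is ambiguous.
- A reader might take the 5% trigger as stated. It is an inference from three sections, though the protocol names no other criterion.
- A reader might take 23% to 64% as an error rate, or apply it to both comparisons. It is the chance of at least one flag under an assumed k and independence, and it fits only the PrEP Champion comparison.
- A reader might infer serious type I inflation, or a threat to the primary endpoints. Step 4 does not support the first, and section 10.5.2 rules out the second.

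Deferral to the SAP does not remove the point. What is deferred is the list of candidates. Selection from that list according to observed imbalance is fixed in the protocol, and a SAP that follows the protocol inherits it.

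**Conclusion.** The point holds as a minor one, confined to secondary endpoint 1. Whether an adjusted refill analysis is run, which covariates it contains, and possibly which effect measure is reported depend on the data. Section 10.5.3 also names a method that does not yield the promised odds ratio.

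In the PrEP Champion comparison the rule would be triggered by chance in about 23%, 40% or 64% of trials. This assumes 5, 10 or 20 independent variables and the inferred 5% criterion. In the delivery comparison the imbalances may be real, and a screen in about 160 women that ignores bars can miss moderate ones. The effect on type I error is small, about 3.5% to 6% under the simulation's assumptions. The harm is an analysis not fixed in advance and a poor way of choosing covariates.

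**What to change.** 1. **Section 10.5.5:** delete the baseline significance tests. Keep the descriptive summaries and, if a measure of balance is wanted, add standardised differences.
2. **Section 10.5.3:** name one model for refills. The ordered logistic model would match the promised odds ratios; in the delivery comparison it should allow for bars. Align the hypothesis in section 9.2, which is worded in terms of the average number of refills. If a difference in means is preferred, name a model for means and drop the odds ratios.
3. **Covariates:** replace the imbalance rule with a short list of baseline variables judged prognostic, fixed in the SAP before enrolment and used whatever the observed balance. Candidates are already collected: the baseline survey in section 4.2 covers demographic and work information, and section 10.5.6 already defines age bands.
4. **Limitation:** state that this adjustment does not fully remove selection among initiators in the workplace versus facility comparison.

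The cost is protocol and SAP wording, with the ethics approval that section 11.3 requires for amendments. No new data are needed. With the model and covariates fixed in advance, chance imbalance can no longer change the analysis.
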